**Methods:**

SCED evaluation will involve multiple baseline and postintervention assessments of a small number of women experiencing IPV (n=6). Participants will be recruited from IPV service organizations across the Greater Toronto Area. SCED will allow for rigorous within-subject comparison, using repeated measurements at multiple time points for 3 primary outcomes (decisional conflict, empowerment to take safety actions, and use of safety strategies) and 2 secondary outcomes (mental health and IPV recurrence). The evaluation will include 5 phases: recruitment, eligibility screening, multiple baseline interviews, intervention (web app delivery), and multiple postintervention assessments. In this paper, we also discuss the development of rigorous protocols for maintaining safety and flexible data collection methods (in person, via telephone, or online).

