**Figure 1. F1:**
[figure not shown]
Overview of a typical single-case experimental design study flow.

SCED has been used in medical, psychological, and behavioral research for decades to better understand the mechanisms of intervention effects. Recently, it has also been used to assess the effectiveness of technology-based interventions in other areas [32], for example, in vulnerable populations such as adolescents experiencing psychological distress [33], individuals with serious mental illness [34,35], adults with severe autism spectrum disorder [36], and young children [37]. The extant literature suggests that SCED is a viable alternative to RCTs, especially for sensitive outcomes, because it allows for closer observation of individuals [38]—something which is critical for ensuring the immediate safety of participants living with IPV [26,27]. However, to the best of our knowledge, this will be the first adaptation of the methodology to IPV studies [32].

To gauge whether SCED is a viable approach for evaluating a web-based safety planning tool for English-speaking women in the GTA, we have established the following study objectives:

To understand whether women who are living with or have recently experienced IPV can be safely engaged for intense follow-up for the purpose of evaluating a safety planning interventionWe hypothesize that our safety protocols and individualized approach will allow for safe participation in the study, as measured by a lack of reportable or adverse events.To examine the preliminary effectiveness of WITHWomen Pathways and our novel safety protocols on 3 primary and 2 secondary outcomes of interestWe hypothesize that within-person changes to decisional conflict and depressive symptoms will show a decrease, whereas empowerment to take safety actions will demonstrate an increase.

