### Preintervention Assessments

As previously discussed, SCED requires the establishment of stability in a given outcome measure prior to intervention delivery [40]. We plan to assess 3 primary outcome measures that align with those assessed by previous RCT safety planning evaluations and are the direct targets of the intervention’s activities: safety self-efficacy, decisional conflict, and confidence in planning (see Table 1). These speak to the goals of safety planning, which are to *prime* those who are currently experiencing IPV to take action to improve their safety, which reflects the often nonlinear paths and ambivalence women feel about extricating themselves from a violent relationship [41,42]. Additionally, we plan to measure 2 secondary outcomes: IPV recurrence and mental health. IPV itself is a secondary outcome because changes in IPV exposure are not necessarily expected, for the reasons mentioned above. While mental health is not directly targeted by intervention activities in WITHWomen Pathways*,* participation in the intervention may secondarily lead to improvements in mental health through help-seeking actions.

**Table 1. T1:** Outcome variables for evaluation of *WITHWomen Pathways*.

Outcome measured	Primary/secondary	Instrument	Reference
Use and perceived helpfulness of safety strategies, service use	Primary	Intimate Partner Violence Strategies Index (adapted)	Goodman et al (2003) [43]
Empowerment related to safety	Primary	MOVERS^a^	Goodman et al (2014) [13]
Decisional conflict	Primary	Decisional Conflict Scale	O’Connor (1995) [12]
Anxiety and depression symptoms	Secondary	PHQ-4^b^	Kroenke et al (2009) [44]
Intimate partner violence	Secondary	Composite Abuse Scale-Short Form	Ford-Gilboe et al (2016) [45]

a MOVERS: Measure of Victim Empowerment Related to Safety.

b PHQ-4: Patient Health Questionnaire-4.

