The baseline interview is designed to last approximately 15 to 20 minutes and will end with a reminder that the participant will complete some of these same measures every 3 to 4 days for the next 2 to 3 weeks until stability is reached. Participants will receive CAD $10 (US $7.15) as an online gift card or through electronic money transfer upon finishing each preintervention interview. Following the established safety protocols for working with those experiencing IPV described above, preintervention baseline assessments can occur via telephone, in person, or via an online survey, using the mode that seems the safest for the participant [46]. For telephone-based assessments, we will also ask the participant before beginning each session if she is in a private space. Whether collected remotely or in person, the SCED data will be recorded via Zoho Survey (Zoho Corporation) and saved directly to a secure Zoho server.

After each participant’s fifth baseline interview, the research team will assess the overall score for each outcome measure. If the participant achieves stability, measured using previously cited criteria wherein at least 85% of preintervention data fall within a 15% range of the median for at least 1 primary outcome measure (Patient Health Questionnaire-4 [PHQ-4], Measure of Victim Empowerment Related to Safety [MOVERS], and Decisional Conflict Scale), they will progress to the intervention interview [47,48]. If stability is not reached after 5 assessments, baseline measurements will continue for 2 more weeks (3 additional baseline measures with CAD $10 (US $7.15) compensation at each assessment) and reassessed. If, at this point, the participant’s outcome measures are deemed stable, they will proceed to the intervention interview. If not, they will still advance to the intervention visit, but their data will not be included in the effectiveness evaluation. Using the standard SCED protocol, these assessments will result in at least 5 but no more than 8 baseline measurements, ensuring that every participant receives the intervention as soon as possible [49].

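### The baseline stability rule counts the PHQ-4 as a primary outcome and leaves out the safety-strategies index, contrary to Table 1 and the abstract

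*Protocol article*

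**What the plan says.** Table 1 of the Protocol article lists three primary measures: the adapted Intimate Partner Violence Strategies Index, the MOVERS and the Decisional Conflict Scale. It lists the PHQ-4 and the Composite Abuse Scale-Short Form as secondary. The abstract (Methods) agrees, naming "3 primary outcomes (decisional conflict, empowerment to take safety actions, and use of safety strategies".

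The prose above Table 1, under Preintervention Assessments, puts mental health in the second tier: "Additionally, we plan to measure 2 secondary outcomes: IPV recurrence and mental health". It explains that the app does not target mental health directly. The same paragraph names the primary measures as "safety self-efficacy, decisional conflict, and confidence in planning (see Table 1".

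Later in that section comes the stability rule. Baseline is stable when "at least 85% of preintervention data fall within a 15% range of the median", and this must hold "for at least 1 primary outcome measure (Patient Health Questionnaire-4 [PHQ-4], Measure of Victim Empowerment Related to Safety [MOVERS], and Decisional Conflict Scale". A woman who is not stable after five assessments has three more. If she is still not stable, "they will still advance to the intervention visit, but their data will not be included in the effectiveness evaluation".

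**The concern.** In this design each woman's baseline is her control, so the rule that certifies a baseline also decides whose data count. The rule calls a secondary measure primary and omits a measure that Table 1 calls primary. Two errors follow. A woman can be admitted on the strength of an outcome the intervention is not directly aimed at, and a woman can be left out although one of her primary outcomes was stable. With six women planned, one misplaced inclusion or exclusion changes a sixth of the evidence. A stable PHQ-4 series also says nothing about whether the baseline for safety strategies, empowerment or decisional conflict can serve as a control.

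**Working it through.** The article gives no figure for how often the rule is met, so there is nothing to reproduce. The main check is to set the places side by side.

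| Measure | Table 1 | Abstract, Methods | Stability rule |
|---|---|---|---|
| Decisional Conflict Scale | primary | primary | counts, called primary |
| MOVERS | primary | primary (empowerment) | counts, called primary |
| Strategies Index (adapted) | primary | primary (safety strategies) | not listed |
| PHQ-4 | secondary | secondary (mental health) | counts, called primary |
| Composite Abuse Scale-Short Form | secondary | secondary (IPV recurrence) | not listed |

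Table 1 and the abstract agree on every row. The rule departs from both on two rows. The prose labels above Table 1 add a further mismatch: decisional conflict maps by name, safety self-efficacy might mean the MOVERS, and confidence in planning has no evident counterpart in the table.

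**What the threshold requires.** The article says "these assessments will result in at least 5 but no more than 8 baseline measurements". At five points, 4/5 = 80% falls short of 85%, so all five must lie in the band. At eight points, 6/8 = 75% fails and 7/8 = 87.5% passes.

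**Two cases under the rule as written.**

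1. All five PHQ-4 scores lie in the band; the MOVERS, Decisional Conflict Scale and Strategies Index do not meet the threshold. One listed measure is stable, so she passes at the fifth assessment and is analysed.
2. The Strategies Index is stable; the three listed measures are not. No listed measure is stable, so she goes on to eight assessments and, if nothing changes, is excluded.

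The recheck after the extended baseline speaks only of outcome measures being deemed stable and does not repeat the one-measure condition. Entry on the PHQ-4 alone is therefore explicit at the fifth assessment and only implied at the eighth.

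**Can the frequency be found?** Let *s* be the chance that one measure is stable at five points, equal for all three listed measures and independent between them (both assumptions). Then

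- P(pass) = 1 − (1 − s)³
- P(PHQ-4 only) = s(1 − s)²

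For s = 0.2: 0.128/0.488 = 26% of passes. For s = 0.7: 0.063/0.973 = 6%.

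Reading the band as ±15% and assuming normal scores with a within-person coefficient of variation (CV) of 10% or 15%, simulation gives s = 0.508 or 0.189, and shares of 14% or 27%. Now let the PHQ-4 be a whole-number score from 0 to 12 (an assumption; the article gives no range), with the other two scales unchanged. The share is then p(1 − s)² / [1 − (1 − p)(1 − s)²], where p is the simulated stability chance for the PHQ-4:

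- Mean 6, CV 10%, p = 0.110: 0.110 × 0.492² / (1 − 0.890 × 0.492²) = 0.027/0.785 = 3%.
- Mean 8, CV 15%, p = 0.314: 0.314 × 0.811² / (1 − 0.686 × 0.811²) = 0.207/0.549 = 38%.

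The answer moves more than tenfold with inputs that the article does not supply.

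**The case against.** The best defence is that this is a preliminary study of six women which disclaims generalizability, puts safe engagement first among its objectives and does not rest its conclusions on significance tests. The three measures in the rule also match the three outcomes given a direction in the study objectives, where "within-person changes to decisional conflict and depressive symptoms will show a decrease, whereas empowerment to take safety actions will demonstrate an increase". The authors may therefore have meant the rule as it stands. That is fair as to intent, but it does not make the PHQ-4 primary in Table 1 or the abstract, and no reason is given for leaving out the Strategies Index.

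Several stronger readings are tempting, and the article does not support them.

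- *The hypotheses are a rival primary list.* They are not labelled primary. The objective above them covers all three primary and both secondary outcomes, and a hypothesis about a secondary outcome contradicts nothing.
- *The Strategies Index may not be measured repeatedly.* The baseline text says that only some measures recur, but the abstract promises repeated measurement of all three primary outcomes.
- *Stability of the index is never examined.* It is absent from the entry rule only. The Data Analysis Plan computes a baseline Tau for each outcome and participant, and the Data Variability section looks at stability and SD within each phase.
- *The authors can choose their headline outcome afterwards.* The analysis plan commits to the same descriptive statistics, plots and Tau measures for every outcome, and nothing shows selective reporting.

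**Conclusion.** The contradiction stands on the face of the article and needs no assumption. The rule names a secondary measure as primary, omits a primary one, and governs inclusion in the effectiveness evaluation. This is a wrongly stated rule, not detail left to a fuller document. Both consequences, entry on the PHQ-4 alone and possible exclusion despite a stable Strategies Index, follow from the text, the first with certainty only at the fifth assessment.

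Its size in practice is unknown. The range of about 3% to 38% of passes rests on assumed variability, independence and PHQ-4 scoring; it shows that the frequency is indeterminate and is not an estimate of bias. Whether any of the four women already analysed is affected cannot be told from the article.

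**What to change.** Settle one primary list and use it everywhere. Table 1 and the abstract already agree, so the natural course is to bring the prose labels and the stability rule into line with them and keep the PHQ-4 secondary.

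Swapping the Strategies Index for the PHQ-4 is not enough. While one stable measure suffices, a woman could still be analysed on two primary outcomes with unstable baselines. It is better to tie inclusion in the effectiveness evaluation to each outcome separately, so that an effect is read only where that same outcome had a stable baseline.

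Do not re-gate the four women whose data have been analysed. The rule also set the length of their baseline, and assessments not taken then cannot be added now; changing who is analysed at this stage would itself be a post hoc selection. Instead, report for each woman which measures met the criterion and at which assessment, and show the results with and without anyone who passed on the PHQ-4 alone.

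The cost is a wording change, a small table and one extra presentation of results. The downside is that some outcome-level results may have to be flagged as lacking a stable baseline.

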To quantify the pre-post changes in outcomes for each participant, we will follow the WWC guidance by calculating Tau-U, a nonparametric effect size metric. Tau-U allows for the estimation of intervention effects while accounting for trends that may be present during the baseline (preintervention) phase [53,54]. For each outcome and participant, we will compute (1) Tau (preintervention, A), to evaluate baseline trend; (2) unadjusted Tau-U (A vs postintervention, B), which compares data points between the baseline and postintervention phases without adjusting for baseline trend; and (3) adjusted Tau-U (A vs B), which corrects for any nonrandom trends in the baseline phase. Consistent with Fingerhut et al [54], our primary aim is not to assess statistical significance, which would be unreliable in small sample size designs such as SCED, but instead to interpret the direction and magnitude of observed effects. We will use previously validated benchmarks to classify effect sizes as small (0.20‐0.59), moderate (0.60‐0.79), or large (≥0.80) [53]. Even small effect sizes will be considered potentially meaningful when supported by consistent patterns observed through visual inspection of the data (see Table 2).

**Table 2. T2:** Five visual analysis measures of comparison typically used for single-case experimental design evaluation.

Measure	Definition
Nonoverlap of all pairs (NAP)	Values from baseline and intervention time points are paired, and a percentage of pairs whose values do not overlap is calculated.
Extended celeration line (ECL)	An NAP that controls for positive trends in the preintervention phase by calculating the proportion of postintervention data points that are above the median trend line plotted from preintervention data.
Improvement rate difference	It is calculated as the difference in the rates of increase in outcome variable data between the preintervention and postintervention phases by dividing the number of “improved data points” by the total number of data points in that phase.
Tau-U	Tau-U adjusted pairs each preintervention and postintervention observation to make n pairs. The number of positive-change, negative-change, and tied pairs is calculated for each outcome variable

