### Data Variability

To address potential variability in the data, our visual analysis will systematically examine the stability of data points within each phase, in addition to the level and trend. This will be supplemented by our calculation of SD for each outcome per participant in both preintervention and postintervention periods. This allows us to assess not only the occurrence of a change but also the consistency of the intervention’s effect, even with variable data in the preintervention or postintervention periods.

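### Baseline stability is decided once per participant, on any one of three scales, so unstable or untested outcomes enter undistinguished and a woman who fails loses all her effectiveness data

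*Protocol article*

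**What the plan says.** All references are to the protocol article.

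- **Preintervention Assessments, principle.** "SCED requires the establishment of stability in a given outcome measure prior to intervention delivery". Stability is framed as a property of an individual outcome.
- **Preintervention Assessments, rule.** After the fifth baseline a woman passes if "at least 85% of preintervention data fall within a 15% range of the median for at least 1 primary outcome measure". The measures named are "Patient Health Questionnaire-4 [PHQ-4], Measure of Victim Empowerment Related to Safety [MOVERS], and Decisional Conflict Scale".
- **Second check.** If she does not pass, 3 more baselines are taken, to a maximum of 8. If at that point her "outcome measures are deemed stable, they will proceed to the intervention interview". The plural leaves open whether one or all measures must be stable.
- **Consequence of failing.** "If not, they will still advance to the intervention visit, but their data will not be included in the effectiveness evaluation".
- **Table 1.** The three primary outcomes are the Strategies Index, MOVERS and the Decisional Conflict Scale. The PHQ-4 and the Composite Abuse Scale-Short Form are secondary.
- **Data Analysis Plan.** "For each outcome and participant, we will compute" baseline Tau, unadjusted Tau-U and adjusted Tau-U. No stability condition is attached.
- **Data Variability.** The analysis is said to assess the consistency of the effect "even with variable data in the preintervention or postintervention periods".

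**The concern.** In this design each woman's baseline is her control, so stability matters for the series being analysed. The rule judges the woman instead, and two consequences follow.

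First, one stable scale opens the effectiveness analysis to all her outcomes. The other two gate scales may be unstable, and two of the five outcomes, including a primary one, are never checked. Because the gate counts the PHQ-4 as primary, a secondary outcome alone can qualify her.

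Second, a woman with no stable gate scale loses every series, including the two that were never tested. Inclusion then depends on the variability of the outcomes under study, and effectiveness is described only in the steadier women. With 6 planned participants, even one such loss is noticeable.

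**Working it through.** The document gives no power, CV or sample size calculation to reproduce. Its own count, 5 + 3 = 8 baselines, is consistent.

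**1. The passages side by side.** The principle is per outcome, the decision is per participant, and the calculation is per outcome and participant without a condition. Gate scales: PHQ-4, MOVERS, Decisional Conflict Scale. Analysed outcomes: those three plus the Strategies Index and the Composite Abuse Scale. So 5 − 3 = 2 outcomes are untested, and only 2 of the 3 gate scales are primary in Table 1.

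**2. Cost of one exclusion.** 1/6 = 16.7% of the planned sample, or 1/4 = 25% of the 4 women who have completed, and up to 5 outcome series each time.

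**3. A one-stage check.** Let p be the assumed chance that one gate scale is stable, with the three scales independent.

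- P(admitted) = 1 − (1 − p)³
- P(at least one gate scale unstable | admitted) = 1 − p³ / [1 − (1 − p)³]
- Share of gate-scale series unstable among the admitted = 1 − p / [1 − (1 − p)³]

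At p = 0.5: P(admitted) = 1 − 0.125 = 0.875. At least one unstable: 1 − 0.125/0.875 = 0.857. Share unstable: 1 − 0.5/0.875 = 0.429.

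**4. The two-stage rule by simulation.** Criterion: "at least 85% of preintervention data fall within a 15% range of the median", read as ±15%, applied at 5 points and, if no scale passes, at 8. Assumptions, none of them in the document: three independent, trend-free, normally distributed scales with a common within-person CV.

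| CV | Admitted | Gate-scale series unstable among admitted | At least 1 of 3 unstable among admitted | At least 1 of 6 women excluded, 1 − admitted⁶ |
|---|---|---|---|---|
| 5% | 100% | 2% | 7% | about 0% |
| 10% | 99% | 42% | 85% | 6% |
| 15% | 72% | 59% | 99% | 86% |
| 20% | 36% | 64% | more than 99% | more than 99% |

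**5. Sensitivity.** With a between-scale correlation of 0.5, CV 10% gives 97% admitted and 39% of series unstable; CV 15% gives about 67% and 57%. If the 15% range means total width rather than ±15%, everything shifts to lower CVs: CV 5% gives 99% admitted and 42% of series unstable, and CV 10% gives 35% admitted.

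**6. Does an unstable baseline produce more false labels?** In the same trend-free model with no effect, 5 baseline points and 8 postintervention points, |Tau| reaches 0.20, the lower bound of the small label, in about 66% of stable series and about 58% of unstable ones at CV 10%. It reaches 0.60 in about 13% and 6%. A tight run of 5 points is often tight by chance.

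**The case against.** The case against a stronger reading is good, and much of it stands.

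- **Baseline as control fails for unstable series.** A reader might infer this and withhold effect-size labels from them. Step 6 does not support it: without trend or effect, stable series earn labels more often. A trending baseline could mislead, but that was not modelled, and the plan already computes baseline Tau and trend-adjusted Tau-U for each series.
- **Unstable outcomes are analysed as if stable.** No sentence says so. The plan graphs every participant and outcome, examines stability within each phase, and reports the SD for each outcome. What is missing from the stated rule is any link between these checks and the criterion that decides inclusion.
- **All five outcomes are admitted.** This is inferred from the analysis of each outcome in each participant. The baseline section says that only some measures are repeated, so five full baseline series are not certain.
- **The 85% and 15% thresholds are wrong.** They are attributed to cited criteria that are not at hand, and this point does not depend on replacing them.
- **Participants have been wrongly dropped.** Nothing in the document shows that anyone was excluded.
- **The stakes are modest.** The trial is described as preliminary and not expected to generalize, statistical significance is not its aim, and the safe-engagement objective is untouched.

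None of this removes the explicit exclusion of whole participants, the disagreement with Table 1, or the conflict with the plan's own claim to handle variable baselines. If the second check means that all measures must be stable, the two checks disagree and the decision is still per participant.

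**Conclusion.** The point holds as a fault in a stated rule and should be fixed; it does not invalidate the trial. Exclusion of the whole participant is explicit. Undistinguished analysis of unstable or untested outcomes is an inference, though the natural one. The two faults trade places as variability grows: near CV 10% almost everyone is admitted with many unstable series, while at CV 15% and above exclusion becomes likely in a sample of 6. At CV 5% both are negligible. These sizes rest on the assumed CV, independence, absence of trend and ±15% reading; the contradictions between sections do not. The direction of any bias in the effect sizes has not been shown.

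**What to change.** Leave the timing of app delivery as written and change only analysis and reporting.

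1. Keep every participant with postintervention data in the effectiveness tables and graphs.
2. Assess the existing criterion separately for each participant and outcome, including the Strategies Index and the Composite Abuse Scale wherever baseline series exist, and show the flag beside the effect size and baseline Tau.
3. Make exclusion of unstable series a sensitivity analysis.
4. Reconcile the list of primary measures in the stability rule with Table 1, and state whether the second check needs one stable measure or all.
5. Because 4 participants have already been analysed, report this as a post hoc change.

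Cost: protocol wording and one extra flag per series, with no new data. The downside is slightly longer reporting and some noisier series on display.
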